## Abstract

**Background:**

Sepsis is still a major public health concern and a medical emergency due to its high morbidity and mortality. Accurate and timely etiology diagnosis is crucial for sepsis management. As an emerging rapid and sensitive pathogen detection tool, digital droplet PCR (ddPCR) has shown promising potential in rapid identification of pathogens and antimicrobial resistance genes. However, the diagnostic value and clinical impact of ddPCR tests remains to be studied in patients with suspected sepsis. PROGRESS trial is aimed to evaluate the clinical effectiveness of a novel ddPCR assay compared with standard practice.

**Methods:**

PROGRESS is a multicenter, open-label, pragmatic randomized controlled trial (pRCT) set in ten hospitals, including departments of infectious disease and intensive care units. In this study, a total of 2292 patients with suspected sepsis will be randomly assigned to two arms: the ddPCR group and the control group with a ratio of 3:1. The primary outcome is the diagnostic efficacy, that is, the sensitivity and specificity of the ddPCR assay compared with the synchronous blood culture. Secondary outcomes include the mortality rates and the mean Sequential Organ Failure Assessment (SOFA) score at follow-up time points, the length of stay in the hospital, the time to directed antimicrobial therapy, duration of broad-spectrum antibiotic use, and the EQ-5D-5L score on day 90.

**Discussion:**

It is the first multicenter pragmatic RCT to explore the diagnostic efficacy and clinical impact of the ddPCR assay in patients with suspected sepsis, taking advantage of both RCT’s ability to establish causality and the feasibility of pragmatic approaches in real-world studies (RWS). This trial will help us to get a comprehensive view of the assay’s capacity for precise diagnosis and treatment of sepsis. It has the potential to monitor the pathogen load change and to guide the antimicrobial therapy, making a beneficial impact on the prognosis of sepsis patients.

*Trial registration*: ClinicalTrial.gov, NCT05190861. Registered January 13, 2022—‘Retrospectively registered’, https://clinicaltrials.gov/ct2/show/NCT05190861.

## Background

Sepsis is life-threatening organ dysfunction caused by a dysregulated host response to infection [1]. It is considered a significant health concern worldwide for its high morbidity and mortality, which is between one in three and one in six [2]. As a medical emergency, early identification and management are crucial to better clinical outcomes. According to the 2021 Surviving Sepsis Campaign (SSC) guidelines, there is a strong recommendation for administering antimicrobials immediately, ideally within one hour for adults with possible septic shock or a high likelihood for sepsis [2]. The delayed initiation of effective antimicrobial therapy results in worsened outcomes [3], antibiotic misuse problems and a heavier health economics burden.

In clinical practice, physicians count on the information of the causative pathogens to start a precise antimicrobial therapy, highlighting the need for rapid and accurate pathogen identification tools. Currently, blood culture (BC) with antimicrobial susceptibility testing (AST) is the gold standard for diagnosing bloodstream infections (BSIs). However, this standard management is limited by a rather longer turnaround time (TAT). It takes around one to three days for the organisms, sometimes 28 days for the tuberculosis, to be cultured on the specific medium and additional one to two days to provide AST results [4, 5]. The sensitivity of the blood culture is relatively low and it can sometimes give false-positive results because of contamination [4, 6].

In addition to optimizing the culture procedure and inventing methods applied to positive blood culture bottles, emerging molecular rapid diagnosis tests (mRDTs) directly using whole blood samples are currently in the ascendant. These methods can be divided into two categories based on the technical principle: the sequencing techniques and the nucleic acid amplification (NAA) techniques. The former, such as metagenomic next-generation sequencing (mNGS) and nanopore sequencing, are capable of providing unbiased pathogen detection, while the latter specifically target and amplify nuclear acid sequence [7]. Most commercialized NAA methods like SeptiFast and Magicplex are based on real-time quantitative PCR in combination with other techniques, and have been able to shorten the TAT to 6–10 h with less hands-on time [6, 8]. However, some have been withdrawn from the market because of the low sensitivity, underlining the challenge in investigation and implementing of such mRDTs [9, 10].

Among the NAA techniques, droplet digital PCR (ddPCR) stands out for its high sensitivity, the ddPCR also has the capability of absolute nucleic acid quantification by counting the number of positive/negative droplets at the end of PCR reaction and applying Poisson statistical analysis without need of external references. It has been applied to quite a lot fields including liquid biopsy and non-invasive prenatal testing. Recently the ddPCR based assays have also shown promising potential in microbial infection for its ability to detect pathogens at a low amount of plasma DNA fragments which is estimated to be as few as 10 colony-forming unit (CFU) per milliliter in about 4 h’ TAT [11–13]. Therefore, the etiological test result could be obtained on the same day as sepsis was first suspected.

There have been many studies exploring the diagnostic efficacy of novel mRDTs in patients with suspected sepsis, and several of the very ddPCR based assays. However, most of them are single-centered observational studies without evaluating clinical impact nor cost effectiveness of such tests [9, 11, 14]. And the proportion of disagreement with the reference test varied across studies, indicating that a huge impediment to sepsis research is the poor homogeneity, which partially explains why many large RCT studies failed to improve the prognosis of sepsis patients [15–18]. Therefore, there is lack of clinical evidence supporting the value of the novel mRDTs currently, so the potential clinical benefits and risks need to be assessed in real world. This trial aims to evaluate the diagnostic efficacy of the ddPCR assay, examine its consistency with conventional BC results, and further exploring the clinical impact and application value in patients with suspected sepsis.

## Methods

### General study design

This trial is a multicenter, open-label randomized control trial recruiting patients with suspected sepsis. Eligible patients will be included after signing the written informed consents. Then, the enrolled patients will be allocated into two parallel arms using stratified block randomization method with a ratio of 3:1. The two groups of participants are those whose pathogen detection will be achieved through both the ddPCR assay and standard microbiological assessments including a synchronous blood culture (experimental group/ ddPCR group), and those being assessed only through standard microbiological assessments including blood culture and other achievable clinical diagnostic methods like mNGS (comparative group/control group). The detailed study flowchart is shown in Fig. 1.

**Fig. 1 Fig1:**
[figure not shown]
Flowchart of PROGRESS trial procedure

### Setting

This multi-center trial is set in the infectious disease departments and ICUs of ten hospitals, which are distributed across five provinces in China: Huashan Hospital Affiliated to Fudan University, Central Hospital of Minhang District, Xinhua Hospital Affiliated to Shanghai Jiao Tong University School of Medicine, and Shanghai Sixth People’s Hospital Affiliated to Shanghai Jiao Tong University School of Medicine in Shanghai; Nanjing Hospital of Chinese Medicine Affiliated to Nanjing University of Chinese Medicine and Wuxi No. 5 People’s Hospital in Jiangsu Province; Ruian People’s Hospital and The First Affiliated Hospital of Wenzhou Medical University in Zhejiang Province; Xiangya Hospital Central South University in Hunan Province; The First Affiliated Hospital of Anhui Medical University in Anhui Province. The Huashan PROGRESS project team is the trial sponsor and is responsible for the design and supervision throughout this trial.

### Study population

Adult patients who meet the inclusion criteria and none of the exclusion criteria will be eligible to participate in this trial (Table 1). They will be enrolled after providing the informed consent to their physician and the Huashan PROGRESS project team.

**Table 1 Tab1:** Inclusion criteria and exclusion criteria

Inclusion criteria: 1. 18 years old or older 2. Meet at least two of SIRS^a^ criteria: ➀ Temperature > 38 ℃ or < 36 ℃ ➁ Heart rate > 90 bpm ➂ Respiratory rate > 20 or PaCO_2_ < 32 mmHg ➃ WBC > 12,000/µL or < 4000/µL or > 10% bands 3. Hospitalized patients who have a diagnostic blood culture drawn on the same day as enrollment (day 0), which is the standard procedure for suspected sepsis 4. Written informed consent signed by the patient or their legal representative Exclusion criteria: 1. Refusal to participate in the study or failure to comply with treatment or follow-up 2. Known pregnancy or lactation 3. The researcher believes that there are any conditions (social or medical) that allow subjects to participate is unsafe. For example, severe anemia or high risk of bleeding, etc., which are not suitable for taking peripheral blood for testing 4. Participating in other clinical studies	

*SIRS*^a^ system inflammatory reaction syndrome

### Randomization

After being enrolled in the trial, participants will be assigned randomly to either the ddPCR group or the control group using the stratified block randomization method. Stratification is designed to balance the two arms for age (< 65 years or ≥ 65 years) and setting (10 medical centers), the two factors that may jeopardize study conclusions. An online random system is built by a third-party company. The system is used to generate and save the random lists by giving separate blocks for each of the twenty combinations in advance. The block width is an integer multiple of 4 since the ratio is 3:1. In order to prevent manipulation of group assignment during recruitment, the specific block size will be disclosed at the end of this trial by the third-party company to the Huashan PROGRESS project team, who generates the allocation sequence after enrollment. Patients will be recruited consecutively and it is competitive enrollment among the medical centers.

### Blinding

There is no blinding in this trial. After randomization, the group information with corresponding procedure is open to the participants, their physicians and the project team. The Huashan PROGRESS project team will have access to the final trial dataset, and investigators from cooperative hospitals will have access to the data from their respective hospitals.

### Diagnostic methods

The ddPCR assay can identify over fifteen pathogens, covering the most common bacteria and fungi in BSIs according to the China Antimicrobial Surveillance Network 2021 Report (CHINET, http://www.chinets.com) [19] and seven antibiotic resistance genes. Droplet digital PCR analysis was performed using a 5-fluorescent-channel droplet digital PCR system (Pilot Gene Technology (Hangzhou) Co., Ltd.).

When evaluating the diagnostic test accuracy of ddPCR method, positive and negative results compared with the reference method (a synchronous blood culture) are defined according to a previous study [20]. The four possible results of the paired tests are in the following: Positive consistency (true positive, TP): In addition to the complete consistency between ddPCR results and the synchronous blood culture results, it also includes three situations: ddPCR results include additional pathogens, ddPCR test and simultaneous blood culture have results in common and both have independent detection of pathogens, ddPCR results are included in the simultaneous blood culture results; Negative inconsistency (false positive, FP): When the synchronized blood culture is negative, the ddPCR assay independently detects pathogens; Positive inconsistency (false negative, FN): When the ddPCR test is negative, the pathogens are independently detected by the synchronous blood culture. Or pathogens are independently detected by the ddPCR test and the synchronous blood culture without overlapping; Negative consistency (true negative, TN): No pathogen is detected by the ddPCR test nor the synchronous blood culture.

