### Sample size calculation

The predicted sample size is calculated to achieve the primary outcome, which is evaluating the diagnostic test accuracy of the ddPCR method (our index test) compared with the reference test.

According to previous published studies evaluating diagnostic accuracy of ddPCR in patients with suspected sepsis, expected test sensitivity (SN) and specificity compared with blood culture are 85% and 75%, respectively according to our pre-test and the previous studies [11, 14]. And the estimated disease prevalence (P), which is the blood culture positive rate in this case, is around 3% to 15% [5, 21, 22]. Therefore, based on the sample size calculation statistical methodology incorporating in the prevalence of disease [23, 24], with a significance ($$\alpha$$) level of 0.05, a 95%CI width of 10% and a prevalence of 3%, the sample size for the experimental group is:$$\mathrm{N}1=\frac{TN+FN}{P}= {Z}\alpha^2/2\frac{SN(1-SN)}{{W}^{2}*P}=1632.$$

Since patients will be allocated into two groups with a ratio of 3:1, the total sample size of the two groups combined is 1632/3*4 = 2176. Assuming a 5% drop-out rate in follow-up, the sample size is calculated to be 2292 patients.

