The PROGRESS trial is a comparative effectiveness research (CER) for the purpose of evaluating an alternative health-care intervention, which, in this case, is the appliance of a rapid ddPCR diagnostic assay. It can also be classified as a practical RCT (pRCT), and the pragmatic approaches are taken in many aspects. Firstly, the inclusion criteria are designed to enroll any adult patient with suspected sepsis who is likely to be provided the intervention, including people who are immune compromised, with multiple morbidities, or over the age of eighty. Secondly, to set the situation as consistent as possible with the real-world condition, we do not interfere with other pathogen tests that clinicians may choose. Microbial examinations like mNGS are accessible to both the experiment group and the control group. Thirdly, except for day 90 follow-up on the phone, the follow-up will be completed during the patients’ hospital stay. Lastly there will be an intention-to-treat analysis using all available data. It not only maintains a relatively high internal authenticity through the randomized controlled trial design, but also takes into account generalizability and feasibility in ‘the real world’ when assessing the benefits of the ddPCR assay [28].

There are also several limitations about this trial. One limitation is that when calculating turnaround time, we assume the availability of the ddPCR assay is equal to that of standard blood culture, and it is not true. The ddPCR assay hasn’t been integrated into the usual clinical procedures. It is only available for twelve hours during the daytime on weekdays because of the limited number of trained staff to run the ddPCR test at this day. We believe next steps for such a novel mRDT will be making the process of handling samples and interpreting results easier to operate, as well as minimizing the need for technical expertise. And we will add the waiting time into the turnaround time in the final analysis when comparing with that of the blood culture. Also, the assay only includes the fifteen most common detected pathogens in BSIs. It cannot investigate unknown emerging pathogens, and the ddPCR panel’s ability to expand is to be studied. Moreover, since it is not a double-blind RCT, bias such as clinical decision-making preferences are inevitable. And as a comparative effectiveness research and a real-world study, statistical methods need to be taken to further control the confounding factors.

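### The primary accuracy table has no rule for contaminated cultures, so an unmatched contaminant is scored as a ddPCR false negative; at 3% positivity the bias passes 10 points only if more than about 12% of positives are such contaminants

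*Protocol article*

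**What the plan says.** The primary outcome is the sensitivity and specificity of ddPCR against the synchronous blood culture (Outcome measures). Diagnostic methods sets out all four cells of the table:

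- True positive: at least one organism in common, even if either test finds others as well.
- False negative: "When the ddPCR test is negative, the pathogens are independently detected by the synchronous blood culture", or both tests positive with no overlap.
- False positive: culture negative, ddPCR positive.
- True negative: both negative.

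The section takes these definitions from a cited earlier study. It mentions no contaminants, clinical adjudication or composite reference.

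Three other statements bear on this:

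- Background, on blood culture: "it can sometimes give false-positive results because of contamination".
- Sample size calculation, on disease prevalence: "which is the blood culture positive rate in this case, is around 3% to 15" per cent. Culture positivity therefore stands for disease.
- Discussion: "the assay only includes the fifteen most common detected pathogens in BSIs". Diagnostic methods puts the panel at more than fifteen.

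**The concern.** The document says that the reference test can be falsely positive, then defines the primary table as if it could not. Suppose a culture grows only a contaminant in a patient without bacteraemia, and ddPCR is correctly negative. As the rule is written, that pair is a false negative. It is also a false negative if ddPCR finds a different organism, because nothing overlaps. Either way the error lowers sensitivity.

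Sensitivity rests on few patients at the planning prevalence, so a small absolute number of such cultures matters.

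Timing is the reason to settle the rule in advance. The Blinding section states "There is no blinding in this trial". By the Background's figures ddPCR takes about 4 hours and culture one to three days, so the ddPCR result will often be known first. If contaminants were sorted out later by people who know it, they could see which calls remove a ddPCR miss, and sensitivity could then be pushed upwards.

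A separate matter is growth of an organism outside the panel. It enters the same false-negative cell as a failure to detect an organism that the panel does cover, so the single sensitivity figure does not separate the two.

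**Working it through.** **Inputs from Sample size calculation.** "expected test sensitivity (SN) and specificity compared with blood culture are 85% and 75%, respectively"; "a 95%CI width of 10% and a prevalence of 3" per cent; alpha 0.05; prevalence range 3% to 15%. The contamination rate and the share of off-panel growth are not in the document and are varied below as assumptions.

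**1. The plan's own figure.** N1 = z² × SN(1 − SN) / (W² × P) = 1.96² × 0.85 × 0.15 / (0.10² × 0.03) = 1632.7, against 1632 stated. Total 1632 / 3 × 4 = 2176, and 2176 / 0.95 = 2291, against 2292 stated. The figure reproduces with W = 0.10 as the half-width; W = 0.05 would give about 6530. The planned margin is therefore ±10 points.

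**2. Expected counts at 3%.** Reference positives: 1632 × 0.03 = 49. Expected false negatives at 85%: 0.15 × 49 ≈ 7.

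**3. Bias model.** Let c be the share of reference positives that are contaminant-only, and q the chance that such a pair is scored true positive because ddPCR reports the same organism. Then

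apparent sensitivity = 0.85(1 − c) + qc, so bias = −(0.85 − q)c.

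The case q = 0 (no contaminant matched) gives the largest bias. Each contaminant among 49 positives then costs 0.85 / 49 = 1.7 points.

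**4. Where the bias reaches 10 points (q = 0).** c = 0.10 / 0.85 = 11.8% of positives, or 0.118 × 49 ≈ 6 patients. As a share of all patients:

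- if the 3% positivity includes the contaminants: 0.118 × 3% = 0.35%;
- if contaminants come on top of 3% true positives: r / (0.03 + r) = 0.118, so r = 0.40%.

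At 15% positivity with contaminants included: 0.118 × 15% = 1.76%.

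**5. Bias in points over assumed rates (q = 0).**

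| Contaminant-only cultures, % of patients | 3% positivity, contaminants included | 3% true positives, contaminants on top | 15% positivity, contaminants included |
|---|---|---|---|
| 0.1 | −2.8 | −2.7 | −0.6 |
| 0.2 | −5.7 | −5.3 | −1.1 |
| 0.5 | −14.2 | −12.1 | −2.8 |
| 1.0 | −28.3 | −21.2 | −5.7 |

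**6. Matched contaminants.** With q = 0.2 the 10-point threshold is 0.10 / 0.65 = 15.4% of positives. With q = 0.4 it is 0.10 / 0.45 = 22.2%.

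**7. Off-panel growth.** If 85% were the sensitivity for on-panel organisms (the document does not say), an off-panel share f gives an all-organism sensitivity of 0.85(1 − f): 80.8%, 76.5% and 68.0% for f = 5%, 10% and 20%. This is a difference between two quantities, not a bias.

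**The case against.** Four arguments carry weight.

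- **The text says pathogens and relies on a cited study.** A reader might infer that the plan counts any growth at all as disease. The document does not say so: contaminants may be removed under the cited definitions, or under a list in a full protocol or laboratory manual that is not shown. This stands against the strong reading. It does not close the gap, because the article writes out all four cells of its primary table and none tells the analyst what to do with a contaminated culture. Even if removal is meant, it is open whether the pair is then dropped or scored as reference-negative.
- **The stated target is comparison with culture.** Measured as agreement with culture, discordance is not bias. That is right for agreement. But the article uses the terms false negative, sensitivity and disease prevalence, and readers will take the estimate as accuracy for bloodstream infection.
- **The planning 85% is itself measured against culture.** It may already include contaminants and off-panel growth. Subtracting contamination from it would then count the same effect twice, and the shortfall from the planning value would be smaller than the table shows. This stands.
- **No unblinded contaminant review is planned.** Correct. The Blinding section concerns openness of group assignment and procedures. The openness is a reason to fix the rule beforehand, not evidence of a flawed step.

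A reader might also infer that off-panel misses bias sensitivity. They do not: failing to find an organism outside the panel is a real limit of the assay, and the Discussion discloses the limited panel.

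**Conclusion.** The point holds as a gap in the definition of the primary outcome. Culture is taken as truth, the protocol acknowledges contamination, and the written rule scores an unmatched contaminant as a ddPCR false negative.

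A reader might conclude that the bias will exceed the planned margin. The document does not support that, because it gives no contamination rate. At 3% positivity the margin is passed only above about 12% of positives (about 6 of 49; 0.35–0.4% of patients). At 0.1–0.2% of patients the loss is about 3–6 points. At 15% positivity about 1.8% of patients would be needed. All these figures assume that ddPCR matches no contaminant and that 85% is free of contamination; relaxing either makes the effect smaller.

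Off-panel organisms are correctly counted as misses in all-organism sensitivity. The remaining weakness is that this figure mixes panel coverage with analytical performance. The change should be made: it is cheap and protects the sole primary outcome.

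**What to change.** 1. Add to Diagnostic methods a definition of probable contaminants based on culture data alone: organism identity and, where more than one set or bottle is drawn, the number positive. The article does not state how many sets are drawn, so the rule must also work for one. If the cited study or the full protocol already has a rule, state it here.
2. Apply the rule before culture records are linked to ddPCR results. Score cultures with only probable contaminants as reference-negative, so that the pair becomes a true negative or a false positive according to ddPCR.
3. Report the version that counts all growth as a sensitivity analysis.
4. Report sensitivity restricted to on-panel organisms beside the all-organism figure, and reconcile the two statements of panel size.

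The cost is one definition, one data step on existing culture reports, and fewer reference positives. If 6 of 49 were reclassified, the half-width at 85% would go from 10.0 points to 1.96 × √(0.85 × 0.15 / 43) = 10.7 points. No extra patients or samples are needed for the step itself.
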